### Season

Blood samples were obtained in spring (April-May), summer (July-September), fall (October-December), and winter (February-March).

### Safety Considerations

It has been suggested that vitamin D supplementation can safely be utilized in pregnancy [22]. Furthermore, our study participants who received treatment had vitamin D deficiency and hence, the risk of hypervitaminosis D was reduced to almost zero. Also, during the screening program, any medical condition or probable side effects of vitamin D detected were promptly recorded and discussed by a qualified medical specialist involved in the study.

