### Clinical Endpoints

Primary endpoints are to find out the beneficiary impact of screening of pregnant women for vitamin D deficiency on pregnancy and neonatal outcomes and assessing the effect of supplementation with vitamin D on these outcomes. In the screening group, within the framework of randomized controlled trial, the endpoint was cord serum concentration of 25(OH)D to compare various doses, regimen, and routes for vitamin D supplementation in pregnancy.

In this regard, primary outcomes are gestational diabetes, preterm delivery, and pregnancy induced hypertension. Secondary outcomes are type of delivery and neonatal outcomes including birth weight (gr); head circumference (cm), height (cm); appearance, pulse, grimace, activity, respiration (APGAR) score 1, 5 minute, icterus, cord falling off time (day), serum calcium concentration (mg/dl), and cord levels of 25(OH)D (ng/ml).

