#### Women With Moderate Vitamin D Deficiency (Group B)

Group B1: Subjects were treated with 50,000 IU oral vitD3 weekly for a total duration of 6 weeks.

Group B2: Subjects were treated with 50,000 IU oral vitD3 weekly for a total duration of 6 weeks and then were on monthly maintenance dose of 50,000 IU vitD3 until delivery.

GroupB3: Subjects were treated with a single dose of intramuscular administration of 300,000 IU vitD3.

GroupA4: Subjects were treated with a single dose of Intramuscular administration of 300,000 IU vitD3 and then were on monthly maintenance dose of 50,000 IU vitD3 until delivery.

Participants were advised to inform the health care provider about any adverse side effect. A fasting blood sample was obtained 3 months after termination of the intervention for those without maintenance vitamin D therapy (groups A1, A3, B1, and B3) and for all those in other groups at delivery. Also, a cord blood sample was obtained from participants. Separated serum samples after centrifugation were transferred to the central laboratory of Masjed-Soleyman. Samples were stored at −80°C and serum concentrations of vitamin D3 were measured at the end of the study.

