### Definition of Study Outcomes

In this study the primary outcome was vitamin D deficiency measured as serum level of 25(OH)D and was categorized as: (1) severe deficient (<10ng/ml), (2) moderate deficient, (10-20ng/ml), and (3) normal status (>20ng/ml) [36].

Our secondary outcomes were as follows: Preterm delivery was considered as birth at less than 37 completed weeks of gestation [37]. Miscarriage was referred to as pregnancy loss prior to 20 weeks from LMP [38]. Preeclampsia was defined as systolic blood pressure >140 mmHg or diastolic blood pressure ≥90 mmHg and 24-hour proteinuria ≥0.3 g, started at >20 weeks [39]. Gestational diabetes mellitus referred to glucose intolerance first detected during pregnancy and was diagnosed according to the *International Association of the Diabetes and Pregnancy Study Groups (IADPSG)* criteria [40]. Premature rupture of membrane was considered as rupture of the fetal membranes before the onset of labor regardless of gestational age [41]. By type of delivery, we meant cesarean section or vaginal delivery. Birth weight (gr) was defined as weight at birth irrespective of gestational age [42].

APGAR score comprises 5 components including *appearance, pulse, grimace, activity, and respiration*, each of which is given a score of 0-2 and reported at 1 and 5 minutes after birth [43]. Neonatal icterus was defined as the yellowish discoloration of skin and sclera by bilirubin, usually first noted in the face and then the body [44]. Cord falling off time (day) is the separation time of remained umbilical cord after birth [45].

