## Discussion

### Principal Findings

Vitamin D deficiency is one of the most prevalent disorders among mothers and children [26]. Although in the past few decades, early diagnosis of vitamin D deficiency and availability of supplementations and treatment modalities have improved the deficiency condition; hypovitaminosis D still exists as a major public health concern associated with significant morbidities in a variety of countries [23]. Unfortunately, among Iranian women who have sunlight exposure deprivation and inadequate dietary vitamin D intake, it is highly prevalent. Reports indicate that 86% of Iranian pregnant women and 75% of their newborns suffer from vitamin D deficiency [46].

Despite the safety of maternal supplementation in preventing vitamin D deficiency during pregnancy, at the moment there is no certain preventive or interventive strategy to ensure maternal vitamin D sufficiency. Therefore, the effect of vitamin D supplementation in pregnant women remains an arguable problem.

In a double-blind randomized clinical trial, Hollis et al [47] determined the safety and efficacy of vitamin D supplementation in pregnant women. In that study, 350 first trimester pregnant women received 400, 2000, or 4000 IU of vitamin D per day until delivery. The relative risk (RR) of vitamin D deficiency was significantly different between the groups receiving 2000 and 400 IU (RR=1.52, 95% CI 1.24-1.86) and the groups receiving the 4000 and 400 IU (RR=1.60, 95% CI 1.32-1.95). Difference was not significant between 4000 and 2000 IU groups (RR=1.06, 95% CI 0.93-1.19). They concluded that vitamin D supplementation of 4000 IU/d for pregnant women is safe and most effective in achieving sufficiency in all women and their neonates, irrespective of race and ethnicity. The optimization of 25(OH)D and 1,25(OH)_2_ D levels was attained without any evidence of hypervitaminosis or increase in adverse side effects during pregnancy.

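### Hypervitaminosis D is dismissed from baseline deficiency alone, and the categorised 25(OH)D outcome has no upper class, so no criterion lets a high value count against an arm

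*Protocol article*

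**What the plan says.** Safety Considerations makes three statements: supplementation in pregnancy has been suggested to be safe (citing a systematic review); "our study participants who received treatment had vitamin D deficiency and hence, the risk of hypervitaminosis D was reduced to almost zero"; and "any medical condition or probable side effects of vitamin D detected were promptly recorded and discussed by a qualified medical specialist".

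Definition of Study Outcomes states: "In this study the primary outcome was vitamin D deficiency measured as serum level of 25(OH)D and was categorized as: (1) severe deficient (<10ng/ml". The scale continues with a moderate class of 10-20 ng/ml and ends at "3) normal status (>20ng/ml) [36". No class or limit lies above that.

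Clinical Endpoints puts it differently for the randomised part: "the endpoint was cord serum concentration of 25(OH)D to compare various doses, regimen, and routes for vitamin D supplementation in pregnancy". It also lists among the neonatal outcomes "serum calcium concentration (mg/dl), and cord levels of 25(OH)D (ng/ml".

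On follow-up, the section on Group B says maternal blood is taken 3 months after treatment ends in the arms without maintenance and at delivery in the others, with cord blood as well. Samples are frozen, and "serum concentrations of vitamin D3 were measured at the end of the study".

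The closing paragraph under Limitations says the results will inform the best supplementation and treatment methods.

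**The concern.** The safety argument rests on where women started, but the exposure in question is what they were given. Deficiency at entry (below 10 ng/ml in Group A, up to 20 ng/ml in Group B) places no upper bound on the level after repeated 50,000 IU tablets or 300,000 IU injections.

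The outcome scale has the same gap. It was built to define deficiency and serves that purpose. Used as an outcome for comparing regimens, it has a floor and no ceiling. A woman just above 20 ng/ml and a woman far above it both score as normal.

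At stake is the claim about the best regimen. The article has a criterion for too little 25(OH)D and none for too much, and it sets the second question aside by an argument that does not hold.

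**Working it through.** The article gives no figure for the risk of hypervitaminosis, so there is nothing to reproduce. Four checks apply.

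**1. The scale.** If an arm's 25(OH)D distribution moves upward, the share above 20 ng/ml can only rise or stay the same. As an illustration, take normal distributions with assumed means and SDs, which are not from the article. Share above 20 = 1 − Φ((20 − mean)/SD):

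| Assumed mean / SD (ng/ml) | Share classed normal |
|---|---|
| 35 / 10 | 93.3% |
| 50 / 15 | 97.7% |
| 70 / 20 | 99.4% |
| 100 / 30 | 99.6% |
| 150 / 45 | 99.8% |

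As concentrations, such arms separate plainly. For means of 35 and 100, SD 30 and 90 women per arm (100 less 10% loss), the standard error is 30 × √(2/90) = 4.47, and 65/4.47 = 14.5, so power is close to 100%. The difference would be visible. What is missing is a statement of what it means.

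**2. Treatment-phase rates.** Inputs are the schedules for Groups A and B and the trials described under Principal Findings. In one, "350 first trimester pregnant women received 400, 2000, or 4000 IU of vitamin D per day until delivery", with no hypervitaminosis reported; another gave 50,000 IU every 2 weeks.

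- Weekly 50,000 IU: 50,000/7 = 7,143 IU/day, which is 7,143/4,000 = 1.8 times the highest daily dose cited.
- 50,000 IU every 2 weeks: 50,000/14 = 3,571 IU/day, so the weekly course is 2.0 times that rate.
- Two injections of 300,000 IU, if both fall within 6 weeks: 600,000/42 = 14,286 IU/day, or 3.6 times 4,000. The wording of the A3 and A4 schedule is ambiguous, and this is one reading of it.
- One 300,000 IU injection: 300,000/4,000 = 75 days at 4,000 IU/day.

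**3. Cumulative dose to delivery.** Assumptions: entry at 9-12 weeks (the interquartile range in Table 4), delivery at 37-40 weeks, a month of 4 to 4.35 weeks, full adherence. Follow-up is then 25-31 weeks, or 175-217 days. At 4,000 IU/day the total is 175 × 4,000 = 700,000 to 217 × 4,000 = 868,000 IU.

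| Arm | Total (IU) |
|---|---|
| A1, A3 | 600,000 |
| A2 | 700,000-800,000 |
| A4 | 800,000-900,000 |
| B1, B3 | 300,000 |
| B2 | 500,000-600,000 |
| Fourth B arm | 550,000-650,000 |

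Matched on duration, six of the eight arms total less than the 4,000 IU/day regimen. A2 and A4 are about equal to it: the lowest ratio is A2 at 31 weeks (800,000/868,000 = 0.92) and the highest is A4 at 25 weeks (800,000/700,000 = 1.14).

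**4. When a high level could be seen.** Treated women have a 25(OH)D value at entry. The next samples are 3 months after treatment or at delivery, and both are assayed at the end of the study. No sample is described soon after an injection, and maternal calcium is not described. A raised level without symptoms therefore could not be detected during treatment, and the late samples would understate any peak.

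**The case against.** The strongest reply is that the three-class scale is not what ranks the regimens. Clinical Endpoints names cord 25(OH)D concentration for that purpose, and Statistical Analysis compares continuous variables by t test or Mann-Whitney. Gestational diabetes, preterm delivery and pregnancy-induced hypertension could each be worse in a larger-dose arm, as could neonatal calcium, icterus or Apgar score, and side effects are reported and recorded. This stands. A reader might infer that over-treatment cannot show, or that the design favours the largest dose by construction. The article does not support either. The argument about scoring applies only to the categorised outcome. That outcome is nevertheless the one called primary under Definition of Study Outcomes, and a test on cord concentration shows only that arms differ, not when a high value is unfavourable.

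A reader might also infer that the regimens lie well above every dose cited. That is true of treatment-phase rates only. Over the whole follow-up most arms total less than the 4,000 IU/day regimen. The safety statement also cites a systematic review whose doses are not shown here, so the cited support cannot be said to stop at 4,000 IU/day.

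Nor do end-of-study assay and prompt recording contradict each other. The recording covers side effects that were detected, and the text never says that raised 25(OH)D was among them.

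Finally, safety tables and thresholds may sit in a full protocol or analysis plan that is not shown, so their absence from an article is no finding. The point here rests on what the article does state: an inference that fails and an outcome scale open at the top.

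**Conclusion.** The concern holds in limited form. The near-nil risk stated under Safety Considerations is not supported by the reason given, because baseline deficiency does not bound the level after treatment. On the categorised 25(OH)D outcome, overshoot scores as normal. Other recorded outcomes could reveal a difference between arms, but the article gives no criterion by which a high 25(OH)D value counts against one, and levels are known only at the end of the study.

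The size is best given as exposure. Treatment-phase rates are 1.8 times the cited 4,000 IU/day for the weekly course and 3.6 times for the two-injection course (on the reading that both fall within 6 weeks). Cumulative totals are below or about equal to that regimen's, under the assumptions listed. Neither figure shows that any regimen is safe or unsafe. No rate of hypervitaminosis can be derived from the document. The gap should be closed before any regimen is called best. It does not invalidate the randomised comparison.

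**What to change.** - Remove the inference from baseline deficiency to near-nil risk under Safety Considerations.
- Add an upper reporting category, with a reference for its cut-off, to the 25(OH)D outcome under Definition of Study Outcomes. Fix it before arm comparisons are seen. The Results section says analysis is under way, and Table 2 already shows vitamin D values for Shushtar, whose samples were to be assayed at the end. If comparisons have been seen, label the cut-off post hoc.
- Report by arm the number above the cut-off and the highest maternal and cord values, beside the proportion above 20 ng/ml. Note that sampling 3 months after treatment or at delivery understates peaks.
- Present that table with any statement about the optimal regimen.
- State under Safety Considerations that prompt recording covers clinical side effects only, not 25(OH)D levels, which are assayed at the end of the study.

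The cost is one category, one table from values already planned, and two changes of wording. The safety statement becomes less reassuring. This is a change to reporting; no dose or clinical rule is proposed.

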### Approval and Ethical considerations

The protocol was approved by the medical ethics committee of the research institute for endocrine sciences of Shahid Beheshti University of Medical Sciences (10ECRIES25/10/92) (Trial Registration: IRCT2014102519660N1). The reviewers’ comments and acceptance letter are provided (see Multimedia Appendices 1-3). Participants were required to sign a written informed consent at recruitment covering all trial procedures and data collection. It was emphasized that participation in the study was voluntary and they were free to withdraw from the study at any time.

## Results

Recruitment commenced in July, 2014 and as estimated, nearly 3.5 years is needed to complete the study. Currently, this study is in the stage of analyzing data.

The baseline characteristics of the study participants are shown in Tables 2 and 3, which indicate no significant difference between the participants of the 2 cities.

**Table 2 table2:** Baseline characteristics of study participants, overall and by study sites.

Characteristics	Masjed-Solayman n=900	Shushtar n=900	Overall n=1800	*P* value^b^
Age (year)	29 (25-32)^a^	29 (25-32)	29 (25-32)	.63
Marriage age (year)	20 (18-22)	19 (17-23)	19 (17-22)	.08
First delivery age (year)	20 (18-22)	20 (18-21)	20 (18-22)	.57
First pregnancy age (year)	21 (19-24)	20 (18-24)	21 (19-24)	.08
Pregnancy week	10 (9-12)	10 (9-12)	9 (10-12)	.07
Gravity	2 (1-3)	2 (1-3)	2 (1-3)	.95
Parity	1 (0-2)	1 (0-2)	1 (0-2)	.86
Number of abortions	0 (0-0)	0 (0-0)	0 (0-0)	.96
Number of children	1 (0-2)	1 (0-2)	1 (0-2)	.79
Vitamin D4 (ng/ml)	11 (7-16)	11 (7-16)	11 (7-16)	.96
SBP (6-10w) (mg/dl)	115 (110-120)	120 (110-120)	120 (110-120)	.87
DPB (6-10w) (mg/dl)	70 (60-70)	70 (70-70)	70 (60-70)	.65
Maternal weight (6-10 w)	65 (59-70)	64 (59-70)	64 (59-70)	.98

^a^Median (interquartile range).

^b^*P* value obtained from independent samples distribution nonparametric Mann-Whitney test (the significance level is <.05).

**Table 3 table3:** Baseline qualitative characteristics of the study participants, overall and by study site.

Participant characteristics		Masjed Solayman		Shushtar		Overall			
		Frequency (n)	Percentage (%)	Frequency (n)	Percentage (%)	Frequency (n)	Percentage (%)	^a^*P* value	

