### The First Phase

In the first phase, pregnant women attending prenatal care centers of urban areas of Masjed-Soleyman and Shushtar were recruited from July 1-September 31, 2014. Due to the blinding purposes and to avoid contacts among study subjects [34], we chose 2 cities with similar cultural, geographic, nutritional habits, and sun exposure conditions; one of these cities was assigned to intervention.

Masjed-Soleyman County is in the northeast of Khuzestan province. Its area is 9/6327 km^2^ with a population of 103,369 people with Persian ethnicity. This is a sunny region with a hot and humid climate. Its altitude is 260 meters above sea level. In terms of geographical location, it is between 31°59′ E longitude and 49°17′ N latitude. Shushtar County is in the north of Khuzestan. Its area is 2436 km^2^ with a population of 192,361 people with Persian ethnicity. The climate is similar to Masjed-Soleyman. Its altitude is 150 meters above sea level. In terms of geographical location, it is between 48°20′ E longitude and 32°30′ N latitude.

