### The Second Phase

In the second phase of the study, to assess the effect of screening strategy on maternal and neonatal outcomes, Masjed-Soleyman participants were assigned to a screening program versus Shushtar participants acting as the nonscreening arm. Within the framework of the screening regimen, an 8-arm blind randomized clinical trial was undertaken to compare the effects of various treatment protocols. Due to the cost and complexity of the process, 800 pregnant women with vitamin D deficiency from Masjed-Soleyman were randomly allocated to 1 of the designed intervention programs according to the study Figure 1. The remaining women with vitamin D deficiency were referred to specialists for further treatments. Participants of Shushtar did not receive any vitamin D supplementation. However, the comparison of the basic confounders between the initial recruited sample in Masjed-Solayman and the women allocated to intervention indicated no statistically significant difference and hence no selection bias occurred during the allocation of treatment (Table 4).

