### Statistical Analysis

Data will be expressed as mean (standard deviation, SD) for normally distributed variables and frequency (%) or median (interquartile range, IQR) for categorical and or nonnormal variables. Continuous variables are checked for normality using the one sample Kolmogorov-Smirnov test. Distribution of variables between the 2 groups is compared using *t* test or Mann-Whitney nonparametric test in case of normality violation and reported as mean (SD). Categorical variables are compared using Pearson and chi-square tests. An intention-to-treat analysis of the results is used. Generalized linear models will be used to assess the relationships between outcomes and exposures (here vitamin D3 supplementation intervention) adjusted by appropriate covariates. Analyses will be performed using the software SPSS version 19 (SPSS Inc). *P* value of less than .05 is considered as significance level.

**Table 1 table1:** The steps of study analysis.

Proceedings		Stage
Obtaining written inform consent form and completing the questionnaire		Recruitment and completion of the questionnaire
Determining groups according to their status of vitamin DCollection of the laboratory samples Obtaining fasting blood samples. Assessment of serum concentration of vitamin D in Masjed-Solayman immediately and storing Shustar samples at −80°C		Classification
Obtaining fasting blood samples 3 months after termination of the intervention for those without maintenance vitamin D therapy (groups A1, A3, B1, and B3) and for all women at delivery time. Obtaining cord blood sample from all participantsStart of intervention Prescription of vitamin D according to various protocols (A1-3 and B1-3) for intervention groups		Replication of laboratory samples
Follow-up of pregnancy outcomes and neonatal calcium and vitamin D status		Follow-up
	
	

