**Spouse education**									
	Illiterate	33	3.70	24	2.70	57	3.20	.01^a^
	Primary	136	15.10	144	16.00	280	15.60	
	Guidance school	178	19.80	207	23.00	385	21.40	
	High school	249	27.70	190	21.10	439	24.40	
	Academic	304	33.80	335	37.20	639	35.50	
	Total	900	100.00	900	100.00	1800	100.00	

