**Accommodation**									
	Apartment	431	47.90	371	41.20	802	44.60	.004^a^
	House	469	52.10	529	58.80	998	55.40	
	Total	900	100.00	900	100.00	1800	100.00	

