**Occupation**										
	Worker	14	1.60	21	2.30	35	1.90	.46
	Clerk	135	15.00	119	13.20	254	14.10	
	Self-employed	111	12.30	117	13.00	228	12.70	
	Housewife	640	71.10	643	71.40	1283	71.30	
	Total	900	100.00	900	100.00	1800	100.00	

^a^The chi-square statistic is significant at the .05 level.

^b^Fisher exact test results is significant at the .05 level.

For the second phase of the study, as statistically was calculated, we needed 800 women, therefore the remaining women were referred to a specialist for further treatments. However, in terms of baseline features except for vitamin D levels, there was no significant difference between the initial sample in Masjed-Soleyman and those who were allocated to intervention (Table 4). The difference for vitamin D is ignorable though.

**Table 4 table4:** Comparison of baseline characteristics between the initial sample of Masjed-Soleyman participants and those allocated to intervention.

Baseline variables	Initial sample (n=1581)	Allocated for intervention (n=900)	*P* value^a^
Age (year)	29 (25-32)^b^	29 (25-32)	.77
First pregnancy age (year)	20 (18-22)	20 (18-22)	.94
First delivery age (year)	20 (18-22)	20 (18-22)	.73
Gestational age (week)	10 (9-12)	10 (9-12)	.97
Vitamin D	11.9 (8-17)	11.2 (7-16)	.01
Number of children	^b^1 (0-2)	1 (0-2)	.67
Gravity	2 (1-3)	2 (1-3)	.62
Parity	1 (0-2)	1 (0-2)	.47
Number of abortions	0 (0-0)	0 (0-0)	.94

^a^*P* value obtained from nonparametric Mann-Whitney test for nonnormal variables.

^b^Median (interquartile range, Q1-Q3).

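### The article declares the two cities balanced at baseline, but its own Table 3 flags six of eleven variables as different; its statement of no selection bias likewise conflicts with Table 4

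*Protocol article*

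**What the plan says.** Two separate statements of comparability are made.

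**Between the cities.** The First Phase explains the choice of sites: "we chose 2 cities with similar cultural, geographic, nutritional habits, and sun exposure conditions". Results then presents Tables 2 and 3 as tables "which indicate no significant difference between the participants of the 2 cities". Statistical Analysis sets the criterion: a P "value of less than .05 is considered as significance level". The Table 3 footnote defines its flag: "The chi-square statistic is significant at the .05 level". Six rows carry that flag, for example "Apartment 431 47.90 371 41.20 802 44.60 .004^a".

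**Within Masjed-Soleyman.** The Second Phase says that the comparison of the initial sample with the women allocated to treatment "indicated no statistically significant difference and hence no selection bias occurred during the allocation of treatment", citing Table 4. The Results text just before Table 4 makes an exception for vitamin D and then adds: "The difference for vitamin D is ignorable though". Table 4 gives vitamin D as 11.9 (8-17) against 11.2 (7-16), P=.01, with column sizes 1581 and 900. The Abstract, The Second Phase and Results all put the number for the intervention at 800.

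Statistical Analysis plans generalized linear models with covariate adjustment and does not list the covariates.

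**The concern.** Masjed-Soleyman is the screening arm and Shushtar the non-screening arm. With one city per arm and no randomisation between them, any city difference that bears on outcome is mixed with the effect of screening. Comparability at baseline and covariate adjustment are the only protections. A sentence declaring no difference removes the stated reason to adjust for the variables that do differ, and several of those plausibly bear on vitamin D status. The effect of screening on pregnancy and neonatal outcomes is listed first among the primary endpoints, so the statement supports a main conclusion of the study.

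The second statement has a different role. It supports the claim that the treated women represent the screened sample. A non-significant test cannot establish absence of selection bias, and here one of the tests is significant.

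**Working it through.** **1. Reproduce Table 3.** Inputs are the printed counts, 900 women per city. With equal groups, Pearson's chi-square without continuity correction reduces to the sum over categories of (a − b)²/(a + b), where a and b are the two city counts.

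- Sun exposure: 55²/583 + 101²/665 + 74²/396 + 82²/156 = 5.19 + 15.34 + 13.83 + 43.10 = 77.46
- Veil: 174²/830 + 174²/970 = 36.48 + 31.21 = 67.69
- Cream: 136²/484 + 65²/707 + 71²/609 = 38.21 + 5.98 + 8.28 = 52.47

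| Variable | Chi-square (df) | Recomputed P | Printed P | Standardised difference |
|---|---|---|---|---|
| Sun exposure | 77.46 (3) | 1.1e-16 | .001, flagged | 0.42 |
| Veil | 67.69 (1) | 1.9e-16 | .001, flagged | 0.40 |
| Cream | 52.47 (2) | 4.0e-12 | .001, flagged | 0.35 |
| Spouse education | 13.27 (4) | .010 | .01, flagged | 0.17 |
| Gloves | 9.15 (1) | .0025 | .002, flagged | 0.14 |
| Accommodation | 8.10 (1) | .0044 | .004, flagged | 0.13 |
| Education | 8.56 (4) | .073 | .07 | 0.14 |
| Spouse occupation | 5.04 (2) | .080 | .08 | 0.11 |
| Sun glass | 2.06 (1) | .151 | .15 | 0.07 |
| Spouse smoke | 1.16 (1) | .281 | .28 | 0.05 |
| Occupation | 2.57 (3) | .462 | .46 | 0.08 |

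All eleven agree with the table; the three entries printed as .001 are in fact below .001. Six of eleven are under .05, and a continuity correction in the two-by-two tables does not change that count.

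**2. Size.** The standardised difference is the multi-category form, with the averaged covariance of the two cities. For veil it is (0.558 − 0.364)/√[(0.364×0.636 + 0.558×0.442)/2] ≈ 0.40. In the top two sun-exposure categories: (161 + 37)/900 = 22.0% in Masjed-Soleyman against (235 + 119)/900 = 39.3% in Shushtar. Chador: 36.4% against 55.8%.

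**3. Chance.** If the eleven tests were independent and null, six or more results under .05 would have probability 5.8e-6. Over all 24 variables of Tables 2 and 3 the figure is 0.00096. These variables are probably correlated, so both are indicative only.

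**4. Table 2.** All 13 P values are .07 or more. Vitamin D is 11 (7-16) in both cities, P=.96. Mann-Whitney P values cannot be recomputed from medians and quartiles.

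**5. Table 4.** The text in The Second Phase (no significant difference), the table (vitamin D P=.01) and the Results text (an exception, then dismissed) cannot all stand. The allocated women came from the initial sample, so the columns appear to overlap, while the Mann-Whitney test assumes independent groups. Overlap also dilutes differences. With 900 of 1581 selected, the mean of the whole minus the mean of the selected is (681/1581) = 43% of the gap between non-selected and selected women. With 800 selected it is 781/1581 = 49%.

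**The case against.** The strongest reply is that the tables are open: all six differences are flagged in print, the vitamin D exception is conceded in Results, and adjusted models are planned. Listing the covariates is commonly left to a fuller plan that is not shown, so its absence is no finding. That stands. What remains is that the article states a conclusion its tables contradict.

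Some stronger readings are tempting and are not supported:

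- **Vitamin D differs between the cities.** A reader might infer this from P=.01, but that figure is from Table 4, within Masjed-Soleyman. Between cities Table 2 gives P=.96. Table 2 uses 900 Masjed-Soleyman women out of a larger sample. If they are the same 900 as in Table 4, which is an inference from the size and the values, the reassurance is weaker, but it is still not evidence of a difference.
- **The between-city effect is confounded, against screening.** The tables show measured imbalance, not established confounding. Shushtar has more reported sun exposure but also more chador use, and the item called cream is not defined as sunscreen. No direction is shown for gestational diabetes, preterm delivery or hypertension.
- **The cities were claimed to be matched on personal habits.** The First Phase says similar, and goes on to describe climate and altitude. Table 3 sits badly with it but does not refute a claim about regional conditions.
- **The Table 4 difference proves biased selection.** Only deficient women were eligible, so some lowering of vitamin D is expected by design.

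**Conclusion.** The Results sentence on between-city balance is correct for Table 2 and wrong for Table 3, where six of eleven variables differ at the article's own significance level and three have standardised differences of 0.35 to 0.42. In a non-randomised comparison of one city with another this is a serious risk of confounding, with the net direction uncertain. The statement in The Second Phase that there was no significant difference, and hence no selection bias, is contradicted by Table 4 and by Results, and the test used could not support it in any case. The count of 900 conflicts with 800 and has to be reconciled. These conclusions rest on the counts in Table 3 being as printed and, for the overlap point, on the allocated women being part of the 1581. Both statements should be corrected before the between-city analysis is reported.

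**What to change.** 1. In Results, limit the statement of no significant difference to Table 2, and report the six Table 3 differences with standardised differences. Print the three .001 entries as <.001.
2. In The Second Phase, remove the inference of no selection bias and reconcile the sentence with Table 4 and the Results text on vitamin D.
3. Reconcile 900 with 800, and say which 900 Masjed-Soleyman women Table 2 describes.
4. Replace Table 4 with a comparison of selected and non-selected deficient women, preferably by severity stratum, using standardised differences. This removes both the overlap and the difference expected from eligibility.
5. Adjust the between-city generalized linear models for the collected sun-exposure, clothing and socioeconomic variables, chosen on subject-matter grounds. Maternal education (P=.07) and spouse occupation (P=.08) belong in the set; picking only variables with P<.05 would repeat the reasoning at fault.
6. State that adjustment cannot remove unmeasured differences between two single cities.

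The cost is wording plus model parameters. The six flagged variables with maternal education and spouse occupation take at most 3 + 1 + 2 + 4 + 1 + 1 + 4 + 2 = 18 as tabulated, against 1800 women in Tables 2 and 3. For an uncommon binary outcome some categories may need to be merged. No new data are needed.
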